## Abstract

**Title:** "Clinical protocol quantification and optimization study of moxibustion to improve cardiorespiratory endurance in the elderly"

**Objective:** To observe the clinical effects of moxibustion in improving cardiorespiratory fitness in apparently healthy older adults; to apply and promote the clinical protocol of moxibustion for tonifying Qi and blood, improving cardiorespiratory fitness in older adults, effectively assisting older adults in maintaining health, improving quality of life, and contributing to elderly care.

**Study Design:** Randomized controlled trial.

**Participants:** Older adults from neighboring communities of the second affiliated hospital of Nanjing University of Chinese Medicine, Jianye District, Nanjing, China.

**Sample Size:** A total of 105 participants for the study on the clinical effects of moxibustion in improving cardiorespiratory fitness, with 35 participants in the moxibustion group, sham moxibustion group, and blank control group, respectively.

**Treatment Protocol:** (1) Moxibustion group: Moxibustion on bilateral Zusanli (ST36), Shenque (CV8), and Guanyuan (CV4) acupoints, 60 minutes per acupoint, once daily, five times a week (with weekends off), for a total of 12 weeks; (2) Sham moxibustion group: Utilization of specially modified moxibustion device to isolate the heat and radiation of moxa burning. Acupoint selection, moxibustion time, and frequency are the same as the moxibustion group; (3) Blank control group: No interventions given.

**Inclusion Criteria:** (1) Age between 60-80 years old. (2) Normal cognition and ability to complete all assessments and treatments. (3) CPET test indicating impaired cardiorespiratory fitness ( $VO_{2peak} < 20\text{ml}\cdot\text{kg}^{-1}\cdot\text{min}^{-1}$  or  $6\text{MWD} \leq 450$  meters).

**Primary Outcome Measures:** (1) Peak Oxygen Uptake ( $VO_{2peak}$ ), (2) Anaerobic Threshold (AT), and (3) serum central carbon metabolites (CCB), including thirty-four CCB-related biomarkers such as adenosine triphosphate (ATP), nicotinamide adenine dinucleotide ( $\text{NAD}^+$ ), pyruvic acid, and acetyl-coenzyme A (Acetyl-CoA).

**Secondary Outcome Measures:** (1) 6-minute walk distance (6MWD), (2) the Short Form 36 Health Survey (SF-36), and the Qi and Blood Status Questionnaire (QBSQ).

**Safety Measures:** During CPET: (1) a drop in blood pressure exceeding the baseline static blood pressure by 20mmHg; (2) pathological Q waves or severe arrhythmias on electrocardiogram (ECG). (3) Severe hypertensive reaction (e.g., systolic blood pressure  $\geq 220\text{mmHg}$ ). During 6MWT: (1) a decrease in  $\text{SpO}_2$  below 85% and sustained; (2) a decrease in systolic blood pressure of  $\geq 20\text{mmHg}$  with an increased heart rate; (3) systolic blood pressure  $\geq 180\text{mmHg}$  or diastolic blood pressure  $\geq 100\text{mmHg}$ . Adverse events related to moxibustion treatment.

**Statistical Analysis:** The primary efficacy indicators will be analyzed using the full analysis set and data collected according to the protocol.

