## **2. Research Objectives**

The primary goal is to apply and promote the clinical protocol of moxibustion for tonifying Qi and Blood, thereby enhancing cardiorespiratory fitness in elderly individuals. The aim is to effectively assist the elderly in maintaining health, improving their quality of life, and contributing to elderly care initiatives. This study intends to observe the variations in primary outcome indicators ( $VO_{2peak}$ , AT value, serum central carbon metabolites, 6MWD, etc.) and adverse events occurring under the intervention of moxibustion. It aims to evaluate its effectiveness and safety.

-----

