#### **(4) Safety Observation**

- During cardiorespiratory exercise tests, if any of the following danger signs appear before the patient reaches symptomatic limits, consider terminating exercise: central nervous system symptoms like dizziness, vertigo, etc. If blood pressure decreases instead of increasing during exercise, dropping more than 20mmHg from

baseline systolic blood pressure. Pathological Q waves or severe arrhythmias on electrocardiogram, such as multiple frequent ventricular arrhythmias. Severe hypertensive response (e.g., systolic blood pressure  $\geq 220$ mmHg).

- During the 6MWT, consider stopping the test if any of the following danger signs appear: suspected angina with chest pain; intolerable shortness of breath; leg spasms or extreme leg muscle fatigue; gait imbalance; pallor, sweating; dizziness or fainting; SpO2 consistently below 85%; systolic blood pressure drops  $\geq 20$ mmHg with an increased heart rate; systolic blood pressure  $\geq 180$ mmHg or diastolic blood pressure  $\geq 100$ mmHg; inability of the participant to continue the test.
- During moxibustion treatment, observe and record any allergic reactions or burn injuries that occur during or after treatment.

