### **(6) Observational Time Points**

- After participants are enrolled, collect basic information (general information, dietary habits, exercise habits, etc.) and baseline measures, including VO2peak, AT, serum CCB, 6MWD, SF-36, and QBSQ;
- After the 4th and 8th weeks of treatment, conduct and record twice interim assessments, including VO2peak, AT, serum CCB, 6MWD, SF-36, and QBSQ;
- At the end of the treatment (12 weeks), collect basic information again (general information, dietary habits, exercise levels, etc.) and outcome indicators, including VO2peak, AT, serum CCB, 6MWD, SF-36, and QBSQ;
- Follow-up until the 24th week, evaluating indicators including VO2peak, AT, 6MWD, SF-36, and QBSQ.

-----

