## **7. Observation of Adverse Events**

### **(1) Definition**

The term "adverse event" encompasses any symptom, syndrome, or disease occurring in patients during clinical research that affects patient health. This also includes clinically relevant situations identified in the laboratory or other diagnostic procedures, requiring unplanned diagnostic or therapeutic measures, resulting in withdrawal from

the study, or showing clinically significant abnormal laboratory test results.

Adverse events may be new diseases; worsening of symptoms or signs related to the treatment status or the disease itself; unrelated to participation in the trial; or a combination of one or more factors. Therefore, the term "adverse event" does not necessarily imply a causal relationship with the trial therapy.

A serious adverse event refers to adverse events occurring at any dose of the study treatment regimen or at any time during the observation period, including those resulting in death; immediate life-threatening situations; hospitalization or prolonged hospital stay; permanent or severe disabilities; overdose-related events; causing cancer; congenital abnormalities; of significant medical importance (referring to events that do not immediately endanger life or cause death or require hospitalization but may harm patients or require measures to prevent one of the defined consequences); requiring medical intervention to prevent permanent damage or harm.

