#### (4) Management of Adverse Events

- **Observation and Recording:** Investigators should request patients to truthfully report changes in their condition after drug administration and avoid leading questions. Any adverse reactions occurring during the trial should be recorded on the "Adverse Event Form," and investigations should be conducted, detailing the process and results of handling until laboratory tests return to normal and symptoms disappear. The follow-up method can vary from hospitalization, outpatient visits, home visits, phone calls, correspondence, etc.
- **Medical Care:** When adverse reactions are discovered, investigators decide on diagnosis and treatment measures based on the condition, and determine whether to discontinue observation. In the case of serious adverse events, the unit conducting the clinical research must take necessary measures immediately to ensure the safety of participants.
- **Reporting:** Investigators complete the "Serious Adverse Event Report Form" and report to the department, medical office, and ethics committee within 24 hours, signing and indicating the date on the report.

-----  

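### The adverse-event collection wording is narrower than the protocol's own definition, and no common enquiry is scheduled, so general adverse events are likely to be under-ascertained in the blank control arm

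*Protocol*

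**What the plan says.** The definition is broad. Protocol section 7(1) covers "any symptom, syndrome, or disease occurring in patients during clinical research that affects patient health", adds that the term "does not necessarily imply a causal relationship with the trial therapy", and defines serious events as those at any dose or "at any time during the observation period". Section 7(3) then grades causality on five levels, the lowest of which is unlikely.

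The collection wording is narrower:

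- Abstract, Safety Measures: after the warning signs for the exercise test and the walk test, the only further item is "Adverse events related to moxibustion treatment".
- Section 6, Safety Observation: "During moxibustion treatment, observe and record any allergic reactions or burn injuries that occur during or after treatment".
- Section 7(4), Management of Adverse Events: "Investigators should request patients to truthfully report changes in their condition after drug administration and avoid leading questions". The recording sentence that follows speaks of adverse reactions, not adverse events.

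The schedule in section 6(6) gives the content of each visit. It says "After the 4th and 8th weeks of treatment, conduct and record twice interim assessments" and names the efficacy measures. The entries for week 12 and week 24 do the same, with general information, diet and exercise added at week 12. None of them mentions adverse events. Section 5 gives the blank control arm no treatment but the same measurement time points as the other two arms.

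**The concern.** Section 7(4) ties the question to the administration of a drug. No drug is given in this trial, and in the blank arm nothing is given at all, so the question has no reference point there. What is then written down is called a reaction, a term that usually implies a suspected link to treatment, whereas the definition requires no such link. Staff who follow the Abstract and section 7(4) literally would collect harms more narrowly than section 7(1) requires.

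This matters because section 2 makes safety an objective and section 11(1) lists a safety analysis. An untreated arm can show how much ordinary illness to expect in people aged 60 to 80, but only if illness is sought there in the same way as in the treated arms. Events that were never elicited cannot be recovered at the analysis stage, so this has to be settled in the protocol and not in a statistical analysis plan.

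**Working it through.** No figure in the protocol depends on this point. The check is a comparison of texts and a count of contacts.

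**Texts side by side**

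| Step | Where | Limited by cause? | Fits the blank arm? |
|---|---|---|---|
| Definition | 7(1) | No, expressly not | Yes |
| Causality grading | 7(3) | No, goes down to unlikely | Yes, though it refers to drugs |
| Safety measure | Abstract | Yes for the treatment item; no for the exercise-test signs | Only the exercise-test signs |
| Session observation | 6, Safety Observation | Limited to allergic reactions and burns | No, there are no sessions |
| Question to participants | 7(4) | Tied to drug administration | No reference point |
| Recording | 7(4) | Says reactions | Yes, it covers the whole trial |
| Scheduled enquiry | 6(6) | None named | None named |

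The first two rows are broad. The rows that tell staff what to look for, ask and record are mostly narrower, and no scheduled enquiry makes up the difference.

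**Contacts at which an event could come to light**

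- Treatment sessions (section 5): 5 per week × 12 weeks = 60 in the moxibustion arm, 60 in the sham arm and 0 in the blank arm.
- Post-baseline assessments (section 6(6), extended to the blank arm by section 5): weeks 4, 8, 12 and 24, so 4 in every arm.
- Total, counting each assessment separately: 60 + 4 = 64, 64 and 4. The ratio of a treated arm to the blank arm is 64 / 4 = 16.
- Up to week 12: 60 + 3 = 63 against 3. After week 12: 1 against 1.

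The imbalance therefore lies wholly within the 12-week treatment period and only between the blank arm and the other two. The contact ratio measures opportunity to notice an event. It does not estimate bias. To size the bias one would need the background event rate and the chance of capture with and without session contact, and the documents give none of these.

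**The case against.** The strongest reply is that this is leftover template wording inside a sound framework.

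- The definition governs, and it is neutral on arm and cause. A scale that reaches unlikely presupposes that such events have already been recorded. No section says that unrelated events are discarded. This stands. A reader might infer that adverse events are captured only when linked to moxibustion, and the text does not support that.
- The blank arm is not out of sight. At the shared visits each exercise test begins with a health screening questionnaire (contents not shown), and the walk test includes a contraindication check and ratings of breathlessness and fatigue. Section 6(5) records medications and reasons for dropout with no limit by arm. This also stands, so it would be wrong to infer that blank controls are never asked, that their count must be close to zero, or that the arm can have no usable rate. But these are safety checks for the test and incidental sources. None is a stated enquiry about illness since the last visit.
- No adverse-event comparison with the blank arm is stated. Section 2 speaks of "adverse events occurring under the intervention of moxibustion", and in section 11(1) the mention of three groups goes with enrolment numbers. This stands, and it limits the point to any such comparison that is made.
- Section 6(6) times the outcome measures, its lists are introduced as inclusive, and an Adverse Event Form that is not shown may carry a visit question. That is possible. Section 7(4) would still need correcting, because it is the protocol's own instruction on what to ask.
- Drug wording recurs in sections 7(3), 8 and 12 and evidently stands for the intervention. Even so, the blank arm has no intervention after which to ask.

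**Conclusion.** The point holds as an internal inconsistency with a practical consequence. The Abstract and section 7(4) do not match the definition in section 7(1), and no common adverse-event enquiry is scheduled. With 60 extra contacts in each of the other two arms, ascertainment of general adverse events in the blank arm is likely to be lower, so a comparison with that arm could be biased towards showing more events under moxibustion or sham. The direction is a reasoned expectation; the size is unknown.

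This rests on two assumptions: that staff follow the written instruction, and that no form outside the protocol already sets a standard question for all arms.

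Moxibustion against sham is not affected by contact frequency. The two arms have the same session schedule, and the session observation rule is taken to apply to sham sessions as well. The efficacy analyses are untouched. The change is worth making because it is cheap and cannot be made after the data are in.

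**What to change.** - **Abstract, Safety Measures:** replace the treatment-related item with all adverse events as defined in section 7(1), with relatedness graded afterwards under section 7(3). Leave the exercise-test signs as they are.
- **Section 7(4):** ask about changes *since the last visit*, and record *adverse events* in place of adverse reactions.
- **Section 6(6):** add one identical, non-leading adverse-event question at weeks 4, 8, 12 and 24 in all three arms. Base any comparison with the blank arm on those answers alone.
- **Session-observed skin reactions:** report these in a separate table for moxibustion against sham, where observation is equal.

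The cost is a wording amendment, with ethics approval as section 12 requires, and one question at four visits that already take place. The small downside is that more unrelated minor events will be recorded in every arm. No treatment or clinical rule changes.

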# **Clinical Research Project Implementation Plan for Moxibustion**

## **Improving Cardiorespiratory Fitness in Older Adults**

### **1. Research Background and Basis**

According to the requirements of the Jiangsu Provincial Administration of Traditional Chinese Medicine's scientific development project (special topic), this project aims to conduct clinical research on the quantification and optimization of the moxibustion protocol for improving cardiorespiratory fitness in elderly individuals.

#### **(1) Domestic and International Research Status and Analysis**

In May 2021, the National Bureau of Statistics released the results of the seventh national population census, revealing that the proportion of elderly people not only surpassed 10% for the first time (reaching 13.5%) but also increased by 4.63 percentage points, indicating an accelerated aging population. It is estimated that during the "14th Five-Year Plan" period, the total population of individuals aged 60 and above will exceed 300 million, accounting for over 20%, marking the stage of moderate aging. Around 2035, the population of individuals aged 60 and above will surpass 400 million, accounting for over 30% of the total population, entering a severe stage of aging. The aging population issue has once again attracted attention across various sectors in China. In the 2022 "Government Work Report," actively addressing population aging, optimizing elderly care services in urban and rural areas, and promoting the high-quality development of the aging industry were highlighted as national strategies. Improving the physiological condition of the elderly and maintaining their health not only enhances their quality of life but also reduces the socioeconomic burden on healthcare.

#### **(2) Declining Cardiorespiratory Fitness in the Elderly Population**

Cardiorespiratory fitness (CRF), also known as "overall fitness," is the body's capacity to intake, transport, and utilize oxygen during a specific workload and is regarded as the most crucial aspect among various indicators of physical health. It is considered the "fifth vital sign" in assessing an individual's overall health status. Generally, higher levels of cardiorespiratory fitness correlate with better health conditions. However, survey data on populations aged 60 and above indicate varying degrees of decline in cardiorespiratory fitness.

From a functional perspective, cardiorespiratory fitness is primarily associated with the functions of the respiratory system, cardiovascular system, and the overall muscular system. The decline in cardiorespiratory fitness among the elderly is directly related to the decline in cardiorespiratory function. With advancing age, the myocardial cells of the elderly gradually atrophy, leading to decreased cardiac contractility and relaxation,

resulting in reduced cardiac function. Structural and functional changes in the respiratory system, such as thinning of alveolar walls, enlargement of alveoli, reduced number of pulmonary capillaries, decreased elasticity of lung tissues, and decreased respiratory muscle function, also contribute to the decline in cardiorespiratory fitness. Moreover, insufficient blood circulation and oxygen utilization in the body are related to factors such as systemic arterial atherosclerosis in the elderly.

The decline in cardiorespiratory fitness is closely linked to deficiency in Qi and Blood in the context of Traditional Chinese Medicine (TCM). Qi and Blood are fundamental substances in the human body's composition and the maintenance of vital life activities. Therefore, the decline in cardiorespiratory fitness is predominantly manifested as a state of deficiency of Qi and Blood and stasis of Qi and Blood.

### **(3) Declining Cardiorespiratory Fitness and its Relation to Various Chronic Diseases and Immune Aging**

Apart from age-related decline, reduced cardiorespiratory fitness is associated with various chronic diseases, lifestyle habits, physical activity, etc. Studies indicate that not only do patients with chronic obstructive pulmonary disease, coronary artery atherosclerotic heart disease, and hypertension experience severe declines in cardiorespiratory fitness, but individuals with metabolic disorders such as diabetes, hyperlipidemia, and osteoporosis, among others, also commonly exhibit decreased cardiorespiratory fitness. Therefore, the decline in cardiorespiratory fitness is both a cause and effect of chronic diseases, accelerating and aggravating their progression, which not only increases the socioeconomic burden but also severely impacts the quality of life of the elderly.

The innate and adaptive immune systems undergo age-related changes and gradually decline with aging, termed immunosenescence. For instance, natural killer (NK) cells in humans undergo significant differentiation with aging. The decline in cardiorespiratory fitness in the elderly also implies an accelerated process of immune aging. The aging immune system reciprocally contributes to the overall aging of the body. Quantification of immunosenescence indicators, such as circulating leukocyte transcriptome analysis, assists in evaluating the body's immune function status, hence becoming a critical target for extending health span and delaying aging.

### **(4) Moxibustion, which tonifies Qi and nourishes blood, contributes to improving cardiorespiratory fitness**

Currently, the primary strategy and method for enhancing and providing cardiorespiratory fitness primarily involve aerobic exercise. This approach is more suitable for athletes and younger individuals. However, for elderly individuals, there exists substantial individual variability in the intensity threshold for aerobic exercise. It becomes challenging to control exercise intensity and volume, thereby inevitably increasing the risk of exercise-related accidents. Hence, there is a necessity to explore

methods that are suitable for improving cardiorespiratory fitness in accordance with the physical characteristics of elderly individuals. Among these, the traditional Chinese medicine technique of moxibustion warrants deeper exploration.

Studies indicate that moxibustion, by warming and promoting circulation, not only facilitates the unblocking of meridians and regulates the circulation of Qi and blood but also warms and nourishes Qi and blood, meeting the needs of the body's organ tissues for Qi and blood. Experimental research demonstrates: moxibustion can prolong exhaustion time in normal rats during exercise; it can alleviate damage to tissues and cells in the liver, heart, skeletal muscles, kidneys, etc., caused by high-intensity exercise, thus alleviating fatigue. Additionally, moxibustion can elevate muscle glycogen and liver glycogen levels in rats during exercise training, ensuring the supply of glucose to tissues such as nerves and muscles during high-intensity exercise, thereby enhancing physical performance. Research on moxibustion's ability to enhance endurance and fatigue resistance demonstrates the clinical value and potential advantages of moxibustion techniques in improving and enhancing cardiorespiratory fitness.

